### Statistical methods and analysis of interventional study

2.8

All data will be summarized using descriptive statistics (i.e. mean ± SEM). Data will be tested for normal distribution using a QQ plot and the Shapiro-Wilk test. Visualization and assessment of normality will be achieved through creation of histograms and boxplots. To determine differences in mean blood lead level over time in hunters who consume harvested meat with lead projectiles versus those with lead-free projectiles, a conditional linear effects model will also be utilized. This model will be similar to the model described in the feasibility analysis. A random intercept will be utilized to account for natural variation in baseline blood lead measurements among hunters. Predictors will include the grouping variable of lead vs. lead-free projectile, time and the interaction of group and time. Since this study is a cross-sectional study design, sequence of cohort (lead vs. lead-free) will also be adjusted for in the analysis. Other factors, such as any exposure to lead ammunition and isotope analysis may also be included as factors in the analysis. Two to three models will be assessed for fit, including a random intercept model, a linear random slope model and a quadratic random slope model if deemed appropriate. Model fit will be assessed using residual diagnostics and visuals such as scatter plots, interaction plots and time plots. Akaike's information criterion (AIC) will also be used to compare model fit. A variogram will be produced to aid in the appropriate identification of the variance-covariance structure and ensure that any unexplained autocorrelation is identified.

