## Introduction

1

As lead is one of the few substances that does not have a safe level of exposure, it is important to minimize all exposure [1], [2]. Hunters can use lead or lead-free bullets [3], and a vast majority choose to use lead bullets [4], [5], primarily because of tradition and the belief that lead bullets are safe. Non-lead projectiles are considered premium ammunition [6], but they are not significantly more expensive in some world areas [7]. There is a correlation between hunters using lead projectiles and elevated lead blood levels [8], [9], [10], however a causal link is unestablished [11]. As lead-shot meat is sold globally, this potential lead contamination is a global health concern [12].

This is a clinical research protocol to determine the feasibility of assessing lead levels in hunters who use lead projectiles. This observational study will determine if it is possible to perform a subsequent interventional blinded controlled study of lead levels in hunters using lead or lead-free projectiles following consumption of self-harvested wild game. The hypothesis for the subsequent study is that minute lead particles from shrapnel dispersed through the animal during harvest are ingested and this exposure results in increased lead blood levels [3]. This current observational study will establish the sample size and washout period for the subsequent interventional study. This observational study will be conducted in compliance with the protocol, Good Clinical Practice Standards, associated regulations and institutional research requirements.

There are three biological compartments where unexcreted lead is stored: blood, soft tissue, and mineralising tissues. After absorption, lead is stored in the blood compartment with a half-life of 28 [13] – 36 [14] days. Lead rapidly disperses into soft tissues post-exposure and in soft-tissues it has a half-life of approximately 40 days [15]. The primary long term repository of lead in the body is mineralizing tissue in bones and teeth [16]. Importantly, these mineralizing tissue stores can be mobilized and increase lead levels in the blood. The long half-life of lead and the dynamic nature of storage with the various compartments present challenges in identifying causal relationships between lead exposure and blood lead levels.

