**Fig. 1 fig1:**
[figure not shown]
**Design of the current feasibility study**. Participants in the current study will harvest deer with standard lead projectiles. A baseline lead measure, a measure immediately after eating the lead-shot meat, and measures at 9, 18 and 27 days. These blood lead levels will allow a model to be built determining appropriate sample size for each potential washout period.

If this current observational study determines that an interventional study is feasible, the subsequent interventional study would randomize hunters into two groups: hunters using lead projectiles and hunters using non-lead projectiles. All hunters would undergo an initial wash-out period and then have baseline blood lead level recorded. Hunters in both cohorts would then eat the harvested meat and blood lead levels would be recorded 2–4 days after eating the self-harvested meat. Hunters would then repeat this process for a replication of 3 times during the year. After one year, the hunter would cross over to the other type of projectile and repeat the entire process again (Fig. 2). This case crossover study would be analyzed utilizing a conditional linear effects model to account for the correlative nature of longitudinal data involving repeated measures. Additionally, this model will allow for other factors to be included in the model, including time-dependent covariates. Additionally it would be possible to use isotope analysis to identify if the lead levels in the blood of participants were primarily from the environment or from the lead projectiles [10], [19]. Fortunately, baseline blood lead levels in New Zealand are similar to levels in other developed countries [20] thus allowing a broad extrapolation of the data generated.

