Formal consenting for the trial will occur via telephone and the study coordinator will work through the form with the participant. Once the pages have all been reviewed the participant will sign the consent form and return the form by mail.3.Collection of study data

Hunters will be instructed to prepare their game in the usual manner. Typically, this involves mincing meat from the front legs of the animals and processing the rear quarters of the animal into larger cuts of meat. The participants will be instructed to text the study coordinator when processing occurs and the study coordinator will confirm receipt of the text message.

Prior to the first meat being eaten from the lead-shot animal, a baseline blood lead level will be measured. When a meal is eaten from the harvested game that involves ≥85 g (∼3/4 cup) of minced meat per person, the participants will be instructed to text the approximate number of servings eaten and notify the study coordinator of having eaten the meal. Between 2 and 4 days after eating the meal, the participant will report to the clinical laboratory in their local area for blood draw and complete blood count measurement. Each day that the participants are eligible for a blood draw they will receive texts from the study coordinator. After completing the blood draw, the participants will text the study coordinator.

Once the data from the clinical laboratory have been collected the participants will be contacted by the study coordinator. The participants will be instructed to report to the clinical laboratory at 9, 18 and 27 days during the abstention period for blood lead measures. Participants will receive a weekly text to remind them about the study. At the clinical laboratory, participants will provide a blood sample and the clinical laboratory will measure lead blood levels and complete blood count according to the standard clinical protocol. These values will be reported to the study coordinator. The study coordinator will maintain records of the results as described in Data Handling and Record Keeping.

During the study the participants will be requested to provide information on any activities that week that may have exposed them to lead such as reloading ammunition or any of the study exclusion criteria.

No biological samples will be retained.4.Analyses and reporting of results

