### Statistical methods and analysis of feasibility study

2.7

All data will be summarized using descriptive statistics (i.e. mean ± SEM). Data will be tested for normal distribution using a QQ plot and the Shapiro-Wilk test. Visualization and assessment of normality will be achieved through creation of histograms and boxplots. The primary dependent variable is mean blood lead level. In order to determine whether there is a difference in the pattern of mean blood lead level over time while accounting for lead exposure, mean blood lead level at baseline, 2–4 days, 9 days, 18 days and 27 days will be analysed using a conditional model that will account for the correlative nature of longitudinal data involving repeated measures taken from the same subject. This model is advantageous for a variety of reasons, including that this approach can handle unbalanced data (missing data at various time points), as well as continuous and discrete predictors. This model will also be able to model covariance structure which is important when handling correlated data. A random intercept will be utilized to account for natural variation in baseline blood lead measurements among hunters. Predictors will include the grouping variable of lead vs. lead-free projectile, time and the interaction of group and time. The interaction term will allow the investigators to identify whether blood lead level changes over time, thereby determining the most appropriate wash-out period. Other factors, such as any exposure to lead ammunition and isotope analysis may be included as factors in the analysis.

Categorical variables will be analyzed using chi-square tests. Variables including (agree to participate in study/decline to participate because of request to abstain/not because of request to abstain) will be used to determine the feasible length of abstaining from eating wild-shot meat. This value is important in determining the washout period for the interventional study. Adjustments using Fisher exact tests will be utilized to account for any cell counts that are 5 or less.

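### Isotope analysis is allowed as a factor in the blood-lead model although it is a consequence of the exposure under test

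*Protocol article*

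**What the plan says.** Section 2.8 commits the interventional model to these terms: "Predictors will include the grouping variable of lead vs. lead-free projectile, time and the interaction of group and time". It adds sequence and a random intercept, and then allows more: "Other factors, such as any exposure to lead ammunition and isotope analysis may also be included as factors in the analysis". Section 2.7 says the same for the feasibility study: "Other factors, such as any exposure to lead ammunition and isotope analysis may be included as factors in the analysis".

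The Introduction, describing the proposed crossover, gives the purpose of the isotope work: "isotope analysis to identify if the lead levels in the blood of participants were primarily from the environment or from the lead projectiles". It also gives the hypothesis for that study: "minute lead particles from shrapnel dispersed through the animal during harvest are ingested and this exposure results in increased lead blood levels".

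Two further places bear on the ammunition factor. Section 2.5 asks participants about "any activities that week that may have exposed them to lead such as reloading ammunition or any of the study exclusion criteria". The Introduction says of the crossover model that "this model will allow for other factors to be included in the model, including time-dependent covariates".

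**The concern.** A covariate in a model for a treatment effect should be fixed before the treatment acts, or at least not be caused by it. By the article's own account, the isotope result records how much of the measured blood lead came from the projectile. It lies downstream of projectile type and is taken from the same blood as the outcome, so it cannot confound the comparison of lead with lead-free projectiles.

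With this marker held fixed, the projectile coefficient compares hunters whose blood lead has the same apparent source. That is a different question from whether lead projectiles raise blood lead. The Discussion relies on the crossover to settle causation, so the projectile contrast is the one that most needs protecting. The AIC comparison in 2.8 is no safeguard: a marker built from the outcome's own lead can improve fit while spoiling the contrast.

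**Working it through.** **Inputs from the article (section 2.6).** Expected difference d = 0.074, SD 0.19, two-sided alpha 0.05, power 0.8, dependent t-test.

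**The plan's own figure.** Exact noncentral-t power for a paired t-test with these inputs is 0.795 at n = 53 and 0.802 at n = 54, so the stated 54 is reproduced. The article gives no figure for any covariate-adjusted analysis. Everything below is illustration under stated assumptions.

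**Check 1: marker of the amount of projectile lead (linear model).**

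- Blood lead = projectile lead + environmental lead, and projectile lead has mean d in the lead arm and 0 otherwise.
- Taking 0.19 as the SD of a difference between two measurements, the variance of one measurement is 0.19²/2 = 0.01805.
- Assume a share q of that variance is variation in projectile lead: v = 0.01805q.
- Marker = projectile lead + error. With equal arms, the total variance of projectile lead is V = v + d²/4. For marker reliability R, the error variance is V(1 − R)/R.
- Given arm, the slope on the marker is λ = v / [v + V(1 − R)/R]. The adjusted projectile coefficient is d(1 − λ).

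Worked example, q = 0.25 and R = 0.5: v = 0.0045125; d²/4 = 0.001369; V = 0.0058815; error variance = 0.0058815; λ = 0.0045125/0.010394 = 0.434. The adjusted coefficient is 0.074 × 0.566 = 0.042, so 57% is retained.

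Percentage of the 0.074 retained:

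| Reliability R | q = 0.1 | q = 0.25 | q = 0.5 |
|---|---|---|---|
| 0.25 | 84 | 80 | 78 |
| 0.5 | 64 | 57 | 54 |
| 0.75 | 37 | 30 | 28 |
| 0.9 | 16 | 13 | 11 |

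The loss runs from about 16% (R = 0.25, q = 0.1) to 89% (R = 0.9, q = 0.5). A simulation with 200,000 draws per setting agrees to within one percentage point.

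**Check 2: marker of the fraction of lead that is projectile lead.** This is a simulated within-hunter crossover with 54 hunters and 3 post-meal draws per arm. Assumed: coefficient of variation of meal lead 1; between-hunter SD of log background 0.4; median background 0.3, 1 or 2 in the units of d. The 54 is borrowed from section 2.6, since the crossover's size is not yet set. The unadjusted effect is 0.074.

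- Residual noise treated as assay error, marker without error: adjusted effect −0.018, 0.001 and 0.006 at backgrounds 0.3, 1 and 2.
- Same, with marker error 0.02 and background 1: 0.012. With error 0.05 and background 2: 0.061, so 0.061/0.074 = 82% is kept.
- Residual noise treated as true variation in background lead: 0.019 to 0.064 at backgrounds 1 and 2, but about 0.09 to 0.10 at background 0.3, above the true value.

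The adjusted coefficient misses 0.074 in every setting. It is usually too small, sometimes of the wrong sign, and in one group of settings too large.

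**The case against.** Four points can fairly be made for the plan.

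1. **The factor is optional.** Both sentences say that it may be included, and nothing makes an adjusted model primary or drops the unadjusted contrast. This stands: the point is a risk that the text permits, not a defect of a committed analysis.

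2. **The current study has no isotope data.** Section 2.3 lists no isotope outcome, section 2.5 says no samples are kept, and section 2.10 describes only lead and blood-count assays. A reader might infer that the meal effect and residual SD passed to the next sample size would be distorted. The documents do not support this, because no isotope assay is described that could supply the covariate. In 2.7 the edit is for consistency.

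3. **Section 2.8 concerns a later, conditional trial.** This is true, but the article does set out that trial's model, and the sentence is likely to be carried forward.

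4. **The ammunition factor is different.** A reader might infer that it too would remove the effect, because it duplicates the projectile arm. The text does not support that. The sentence concerns factors other than the group term. Read with the question about reloading in 2.5 and the mention of time-dependent covariates in the Introduction, it most naturally means non-meal exposure, which is a legitimate covariate.
   - In simulation with an assumed own effect of 0.05, a separate exposure equally common in both arms leaves the projectile coefficient at 0.075 with or without adjustment.
   - If the exposure is 25, 50 or 80 percentage points more common in the lead arm, the unadjusted coefficient is 0.086, 0.099 or 0.114. The adjusted one is 0.073 to 0.074, with standard errors 1.04, 1.16 and 1.66 times as large.
   - Only if the factor counts the assigned projectile itself does it nearly duplicate the arm. If every lead-arm hunter and a fraction p of lead-free hunters are exposed, the squared correlation with arm is (1 − p)/(1 + p), and the variance rises by (1 + p)/(2p): 5.5, 3 and 1.5 times at p = 0.1, 0.2 and 0.5. That is lost precision, not a removed effect, and it does not apply in 2.7, where all hunters use lead.

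**Conclusion.** The point holds for isotope analysis. By the article's own description it is a post-exposure marker of projectile lead in the blood and does not belong as a covariate beside the projectile term. If it were entered, the coefficient would no longer estimate the projectile effect.

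The size cannot be fixed from the documents. Check 1 gives a loss of about 16% to 89%, resting on assumed marker reliability (0.25 to 0.9) and an assumed share of variance from projectile lead (0.1 to 0.5). A reader might infer that the effect is bound to vanish or always shrink. Check 2 shows that this is not so: one setting keeps 82%, and low background lead with true background variation overstates the effect.

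The consequence falls mainly on the proposed interventional study. For the ammunition factor, only an undefined term remains, which is a matter of wording.

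**What to change.** - In 2.7 and 2.8, delete isotope analysis from the list of possible model factors.
- State that any isotope result will be analysed as a separate outcome, source of lead by arm, which is the use the Introduction gives it.
- As a clarification only, define the ammunition factor as lead exposure other than the assigned projectile and the study meal, such as the reloading activities already asked about in 2.5, entered as a time-varying covariate.

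The cost is one sentence in each of two sections, with no new data. The small downside is that source attribution is reported beside the effect model and not within it.

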### Missing data

2.9

To limit bias, this study will be guided and analyzed under the intention to treat principle, in that all participants will remain in the analysis regardless of missing data. The restricted maximum likelihood (REML) will facilitate the proper handling of unbalanced data or missing data, as well as mistimed measurements, so as to use the collected data in the most efficient way.

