This current study establishes the parameters necessary to assess whether hunters eating meat shot with lead projectiles have elevated blood lead levels. For this feasibility study, hunters will be asked to abstain from consuming meat harvested with lead projectiles for 7 days. After 7 days, hunters will provide a baseline blood sample. Hunters will then consume meat that was harvested with lead projectiles and provide an additional blood sample 2–4 days (the blood-lead level peak post exposure [17]) after consumption. Hunters will also provide subsequent blood samples at periods of 9, 18, and 27 days. During the 27 day period, hunters will not consume meat harvested with lead projectiles. (Fig. 1). We have chosen to use deer as the species for this study to reduce variation; New Zealand is the ideal place to conduct this study because of year-round hunting of deer [18]. This study design will allow for the development of a conditional linear effects model, which will account for the inherent correlation of longitudinal data that involves repeated measures on the same subject over a period of time. A conditional model will also be more robust to any missing data that may arise through the course of the study, which may also facilitate a reduction in the required number of subjects necessary for this feasibility study.

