### Ethics and dissemination

2.10

All data will be collected and managed by the clinical study coordinator. The data will be kept in a password protected database and a key to participant identifying information will be kept in a separate password protected file.

Blood draws will be collected by an independent contract clinical laboratory (MedLab). Blood samples will be analyzed for lead and complete blood count will be performed by the contract laboratory. Those blood data and time of the blood draw will be kept in the anonymized database. If requested by participants, their lead levels will be shared with them. In the event that the participant lead levels exceed 10 μg/dl (the standard level of concern in Australia and New Zealand) participants will be notified immediately with the recommendation to contact their general practitioner. These participants will not be withdrawn from the study.

Consent forms will be maintained in an alternate password-protected database with identifying information. Photographs of the animal harvested will be maintained in the anonymized database. All consented participants will be texted weekly and called monthly to determine if they have had a meal of harvested meat that week and if they have reported for the blood draw. Participant confidentiality will be maintained through a password protected database with a separate key to identify the anonymized data. Records of the study will be retained for 10 years and anonymized data will be deposited in a publicly-available repository.

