**Fig. 5 fig5:**
[figure not shown]
**Expected results from the blood lead level measures.** Following the washout period and baseline blood lead level measurement participants will eat their lead-shot deer. Two to four days after eating lead-shot deer be asked to abstain from eating lead-shot meat and blood lead levels will be assed at 9, 18 and 27 days. These blood lead levels will allow the sample size calculation, based on the three potential washout periods, for a subsequent interventional study to be calculated.

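### The washout estimate is not tied to actual abstention: intention to treat keeps everyone in, the model uses labelled days, and the start of abstention is described in three ways

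*Protocol article*

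**What the plan says.** Section 2.1 makes the washout period, with the sample size of the next study, the primary objective. Section 2.2 defines period 2 as hunters who have abstained for specific lengths of time, and Section 3 speaks of blood levels from people abstaining for 9, 18 and 27 days.

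On the analysis set, Section 2.9 says the study will be "analyzed under the intention to treat principle, in that all participants will remain in the analysis regardless of missing data". It adds that REML will deal with missing data, "as well as mistimed measurements".

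On the model, Section 2.7 says that "mean blood lead level at baseline, 2–4 days, 9 days, 18 days and 27 days will be analysed using a conditional model". Its predictors are projectile group, time and their interaction. Exposure to lead ammunition is a factor that may be added; further lead-shot meals are not named.

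On the start of abstention there are three descriptions:
- Introduction: "During the 27 day period, hunters will not consume meat harvested with lead projectiles".
- Fig. 5 legend: "Two to four days after eating lead-shot deer be asked to abstain from eating lead-shot meat".
- Section 2.5, step 3: "Once the data from the clinical laboratory have been collected the participants will be contacted by the study coordinator", after which they are told to attend for draws at 9, 18 and 27 days within the abstention period.

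Section 2.5, step 2, lets a hunter who declines the full length join for 9 days of abstention or for the longest time acceptable to that hunter. Step 3 gives the three later draws without exception.

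On data capture, Section 2.10 says: "Those blood data and time of the blood draw will be kept in the anonymized database". Participants are also "texted weekly and called monthly to determine if they have had a meal of harvested meat that week".

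**The concern.** A washout period is an elimination quantity. It has to be estimated from samples taken while the person was really abstaining, on a time scale that runs from the last exposure. Intention to treat answers a different question: it preserves the groups formed by randomisation, and this study has none. Keeping everyone in, with the samples labelled day 9, 18 or 27, allows blood drawn after another lead-shot meal to enter the curve as if it were washout.

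The design makes such samples plausible. A hunter who agreed to only 9 days may be eating lead-shot meat again before days 18 and 27. On two of the three descriptions of the start, there is also an interval after the test meal in which further meals are not clearly ruled out.

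Lapse meals lift the later means and make elimination look slower. An unclear day 0 means that the residual attached to 9, 18 or 27 days may belong to another length of time. Both feed into the washout and sample size of the crossover trial.

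**Working it through.** **The plan's own figure.** The only sample size is 54 (Section 2.6: difference 0.074, SD 0.19, power 0.80, two-sided alpha 0.05, paired t-test). Exact noncentral-t power gives n = 54 with power 0.802, so it reproduces. This point does not rest on an arithmetic error.

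**Inputs for the illustration.** Blood half-life 28 to 36 days (Introduction). The documents give no lapse rate; I assume 10%, 20% and 30%. I also assume first-order decay of the meal-related rise and one lapse meal with the same effect as the test meal.

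**Lapse at mid-period (day 13.5), half-life 28 days.**

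Residual at day 27 = 2^(−27/28) + p × 2^(−13.5/28) = 0.513 + p × 0.716.

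Apparent half-life = 27 × ln 2 / (−ln residual).

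| Share lapsing p | Day-27 residual | Apparent half-life |
|---|---|---|
| 0 | 0.513 | 28 days |
| 0.10 | 0.584 | 34.8 days |
| 0.20 | 0.656 | 44.3 days |
| 0.30 | 0.727 | 58.8 days |

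**Sensitivity to timing and half-life.** Let the lapse fall at a uniformly random time from day 0 to two days before the draw.
- Half-life 28 days: residuals at day 27 are 0.583, 0.654 and 0.725, and apparent half-lives 34.7, 44.1 and 58.3 days, so the mid-period choice hardly matters.
- Half-life 36 days: the true residual is 0.595; it reads 0.671, 0.747 and 0.824, with apparent half-lives of 46.9, 64.3 and 96.5 days.
- At 20% lapsing, the share of the true day-27 decline that is hidden is (0.654 − 0.513)/(1 − 0.513) = 29% for 28 days and (0.747 − 0.595)/(1 − 0.595) = 38% for 36 days.

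**Shift of day 0, with no lapses.** If the count starts 4 days after the meal (the latest first draw), the residuals relative to the meal at nominal days 9, 18 and 27, with a 28-day half-life, are 2^(−13/28) = 0.725, 2^(−22/28) = 0.580 and 2^(−31/28) = 0.464, instead of 0.800, 0.640 and 0.513. If it starts at a contact 11 days after the meal (4 days plus an assumed 7 for results), nominal day 9 is really day 20, and 2^(−20/28) = 0.61 remains, not 0.80.

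The slope is not affected by a shift that is the same for everyone: the ratio of day 27 to day 9 is 2^(−18/28) = 0.64 in each case. What is misstated is the residual attached to each nominal washout length. A shift that differs between people adds error as well.

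**The case against.** Several stronger readings are tempting, and the documents do not support them.

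- A reader might infer that the protocol counts draws after a lapse as abstention. No section says so. The sentence in Section 2.9 concerns missing data, and Sections 2.1, 2.2 and 3 all describe the target as samples from people who abstained.
- A reader might infer that abstention is requested only after the first draw or the laboratory result. Section 2.5, step 2, raises it in the first telephone call, before formal consent, and the Introduction excludes lead-shot meat for the whole 27 days. Step 3 does not say that abstention begins at the later contact.
- A reader might infer that nominal days are fixed as the time scale. Draw times are stored, mistimed draws are mentioned, and Section 2.7 allows continuous predictors.
- A reader might infer that an uncertain day 0 by itself distorts the half-life. Under first-order decay a common shift does not.

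It is also fair to say that Section 2.7 speaks of accounting for lead exposure, that exposure information is requested during the study, that compliance is a secondary outcome, and that a detailed rule for lapses is something an article may leave to the full protocol or analysis plan. The lapse shares, the equal meal and the 7-day laboratory delay are assumptions.

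These points narrow the concern but do not remove it. The article does state a principle for the analysis set, and that principle does not fit the primary objective. REML is an estimation method: it deals with mistimed draws only if actual time enters the model, and it cannot recognise a further meal. Recording lapses and reporting compliance do not correct the curve. The three descriptions of the start are a conflict within the text, not an omitted detail.

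**Conclusion.** The concern holds as a risk left open on the primary objective, not as a stated misclassification. Intention to treat is the wrong principle for a non-randomised washout estimate, the model as described has no term for further lead-shot meals, and the text does not give one start for abstention and the day count. If 10% to 30% of hunters ate one equal extra meal and stayed in the curve, the apparent half-life would be about 35 to 59 days when the truth is 28, and about 47 to 97 days when the truth is 36. These sizes depend on the assumed lapse shares, equal meals and first-order decay; with no lapses this part of the bias is nil. The change is worth making before analysis, since it is cheap and most of the data are already to be collected.

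**What to change.** 1. Reconcile the Introduction, Section 2.5 (steps 2 and 3) and the Fig. 5 legend so that the start of abstention and day 0 for the 9-, 18- and 27-day draws are stated once and consistently, and say which draws apply to hunters who agree to a shorter abstention.
2. In Section 2.7, for the washout estimate, use actual days since the last reported lead-shot meal as the time variable, from the stored draw times and reported meals.
3. In Section 2.9, replace intention to treat for this estimate: censor a participant's draws from the first reported lead-shot meal, or listed lead exposure, during abstention. Show the analysis of all participants and all draws as supportive.
4. Count lapses under the compliance outcome.

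Cost: mostly wording, but not only that. As described, the weekly text asks about harvested meat in that week; it would have to ask for the date of the meal and the type of projectile. Late samples will be lost, and more than a few if lapses are common: 68 recruited less 25% leaves 51, and losing 30% of those leaves about 36 (51 × 0.70 = 35.7) against the 54 planned. Censoring may also select the more compliant hunters or those who eat game less often, which is why the all-participants analysis should stand beside it.
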